## Abstract

**Background:**

This study explores the treatment of internal carotid artery stenosis in patients with a high risk for cardiovascular events. The use of regional anesthesia permits ongoing neurological monitoring and enhances patient safety during the procedure. However, the operation can be stressful and lengthy, highlighting the need for strategies to alleviate patient discomfort. This study evaluates audiovisual distractions such as video goggles to potentially improve patient experiences during carotid surgeries, a topic that has not yet been comprehensively researched.

**Objective:**

We aimed to (1) determine whether there is a benefit for patients regarding stress reduction when using video goggles during vascular surgery of the carotid artery and (2) determine whether any parameters can effectively measure such a potential benefit.

**Methods:**

This prospective, randomized study at the University Hospital Augsburg is evaluating the use of HappyMed video goggles by patients undergoing carotid endarterectomy under regional anesthesia. Participants are randomized into either the intervention group, which receives the video goggles, or the control group, which does not. The surgical and anesthetic procedures remain consistent across both groups. Patients are eligible if they meet the surgical criteria, are able to lie supine, and are cooperative. Patients are excluded if they are receiving corticosteroids, have dementia, or have a language barrier. The study uses questionnaires and vital/laboratory parameters, including cortisol levels and heart rate, to assess stress and anxiety. To monitor potential motion sickness, the occurrence of nausea or vomiting is documented. Both patients and surgical staff will evaluate the experience postoperatively to determine the goggles’ impact on patient experience and stress management during surgery.

**Results:**

The study has been approved by the local ethics committee and is registered at ClinicalTrials.gov. Patient inclusion started in September 2022 and should be completed within 3 to 4 years. This paper presents a study protocol that was finalized and approved by the local ethics committee in September 2022. At the time of this protocol’s final submission for publication, approximately 90% of the recruitment had been completed. Following completion of recruitment and data acquisition, the results are intended to be published within one year.

**Conclusions:**

This study aims to improve patient comfort and perioperative care during vascular surgery. Therefore, our study aims to investigate if the use of video goggles during surgery is feasible and if there are parameters that indicate a benefit for patients. This study is being conducted as a pilot trial to provide a foundation for future research aimed at improving patient comfort during carotid artery surgery under local anesthesia.

**Trial Registration:**

ClinicalTrials.gov NCT06704230; https://clinicaltrials.gov/study/NCT06704230

**International Registered Report Identifier (IRRID):**

DERR1-10.2196/70597

## Introduction

Atherosclerosis and macroangiopathy of the internal carotid artery are common conditions in patients with elevated cardiovascular risk. Treatment of internal carotid artery stenosis is often conservative, involving risk factor modification and medication. However, when a certain degree of stenosis is reached or symptoms suggestive of stroke are present, thrombendarteriectomy and revascularization is indicated. Revascularization can be performed either through interventional angiography with stent placement or open surgical endarterectomy [1-3]. The operation is frequently carried out under regional plexus anesthesia, which allows the patient to be awake and enables continuous neuromonitoring. This approach offers the advantage of monitoring for neurological changes during carotid artery clamping, allowing the surgical team to immediately respond, for example, by placing a shunt system to ensure cerebral antegrade perfusion [4]. As a result, regional anesthesia provides a benefit during surgery. However, for patients, the procedure, which can last up to 2 hours or more in some cases, may pose a significant burden. The fixed position, inability to move, sterile drapes over the face, manipulation by the surgical team, and anxiety about potential complications are just a few of the factors that may distress patients during this operation [4]. All in all, studies of operations with local or general anesthesia show that neither technique has any advantage over the other [4]. Both types are carried out frequently. Increased sweating and reports of substantial subjective distress are not uncommon if the procedure is performed under local anesthesia. To the authors’ knowledge, there have been no previous attempts to quantify stress parameters or to reduce stress in these patients.

In many medical fields, devices and therapies are now being used to reduce patient stress in the perioperative setting. In procedures performed under local or regional anesthesia, such as in orthopedics or dentistry, efforts are being made to make operations more tolerable and less stressful for patients [5-7]. For example, music and video goggles can be used to entertain and distract patients during the intervention. Several studies have shown that music can significantly reduce patients’ anxiety, stress, and perception of pain [6,8]. These applications, however, are often limited to dental or pediatric patients [9,10]. In these patient groups, a need for anxiety reduction is understandable, as many individuals find dental treatment stressful. Nonpharmacological sedation or improving the experience for children is highly justifiable. Newer approaches using video goggles appear in more and more fields, but good systematic randomized studies have not yet been performed. In vascular surgery, particularly carotid surgery, the use of audiovisual distraction during the procedure has not been implemented, to our knowledge, and its potential benefits remain undocumented. Because of the special setting of the surgery and the burden on patients, it is necessary to analyze the use of audiovisual distraction devices in carotid surgery. This study aims to demonstrate the feasibility and potential patient benefit of using video goggles in vascular surgery, particularly during carotid procedures. Additionally, we seek to assess a range of parameters that may be suitable for capturing such effects.

## Methods

### Trial Design and Study Population

In this prospective, randomized study, the use of the HappyMed video goggles (HappyMed GmbH) will be evaluated in patients undergoing carotid endarterectomy under regional anesthesia. The study is being conducted as a single-center study at the University Hospital Augsburg (Augsburg, Germany) in collaboration with the departments of vascular surgery and anesthesiology. Patient acquisition started in September 2022 and should be completed within three years. All patients scheduled for the abovementioned procedure who meet the inclusion criteria are informed about the study and invited to participate. Upon agreeing to participate, patients are randomized according to a predefined list, assigning them to either the intervention group (with video goggles) or control group (without video goggles). The surgical procedure is identical for both groups, and the study does not influence the operative or anesthetic management of the patients.

### Ethical Considerations

Informed consent for the study is obtained during preoperative preparation, separate from the surgical consent process, to ensure that patients clearly distinguish between their participation in the study and the surgical procedure. The study was submitted to the responsible ethics committee (Ethikkommission Ludwig Maximilians Universität München, Germany) for review and has been approved (reference number 21-1199). Both the sponsor (University Hospital Augsburg) and the funder (HappyMed GmbH) have no direct influence on data management or the publication of the study results. All data are fully anonymized and treated confidentially; no data will be shared with third parties. No compensation was provided to participants.

### Inclusion Criteria

Patients are included who undergo carotid endarterectomy under regional anesthesia. For anesthesia, a cervical block is used. To qualify for the study, patients must meet the clinical requirements for the surgery, be sufficiently oriented and cooperative, and be able to lie supine for the duration of the procedure.

### Exclusion Criteria

Exclusion criteria include current corticosteroid use or medications affecting cortisol levels, as well as patients with insurmountable language barriers that would impair understanding of the questionnaire. Additionally, patients with severe dementia or lacking the capacity to provide informed consent are excluded.

### Secondary Exclusion Criteria and Adverse Events

Patients who withdraw consent after enrollment will be excluded from the study. If complications arise during surgery requiring conversion to general anesthesia, patients will also be excluded.

### Randomization

Patient randomization follows a predefined list based on patient ID, assigning them to either the control or intervention group. The list is followed sequentially, and random assignment to either the intervention or control group is performed using Microsoft Excel. The randomization scheme is constructed to ensure a 1:1 allocation ratio (50-50) upon reaching a total sample size of 100 patients. Due to the nature of the intervention, blinding of participants and investigators is not feasible.

### Sample Size Estimation

Due to the exploratory nature of the study, no formal sample size estimation was performed. There are no other studies covering this topic. Therefore, there are no data available on how great a relevant effect should be, nor on how large the sample size should be. The goal is to use this study and its preliminary results as a basis for initiating a confirmatory trial. With a sample size of 100 patients, the sample should be big enough to provide an overview on the possible characteristic values.

### Interventions

The intervention group will receive perioperative video goggles with an audio system designed to distract patients from the surgical process and enhance their experience. The video goggles will display various nature scenes accompanied by soft music. Patients can choose from a variety of preloaded content. The device meets the requirements of the Medical Device Directive 93/42/EWG and the Austrian Medical Devices Act. The anesthesiologists, who are primarily responsible for helping the patients use the goggles, received brief online training on how to operate the device. To minimize potential confounding factors, intraoperative management is performed by a small and experienced team of anesthesiologists. Figure 1 shows the timing and parameters that will be measured during surgery.

**Figure 1 figure1:**
[figure not shown]
Timing and measured parameters during surgery. The intervention group uses the goggles during the time indicated by the red line. KAB: Kurzfragebogen zur aktuellen Beanspruchung (German for “short questionnaire for acute stress”); OR: operation room; RASS: Richmond Agitation Sedation Score; STAI: State-Trait Anxiety Inventory.

### Assessment of Distress

To assess patient stress, questionnaires and vital/laboratory parameters will be used. The day before surgery, after they provide informed consent, the patients will complete initial questionnaires. These include the Spielberger State-Trait Anxiety Inventory (STAI; Hogrefe Verlag), which measures both “trait anxiety” (a general predisposition to anxiety) and “state anxiety” (anxiety related to the current situation, ie, the upcoming surgery) [11]. This questionnaire is often used to measure anxiety and is seen as an indicator of distress. The score is used in many types of analysis, although the trait sections of the STAI are believed to measure negative affectivity rather than trait anxiety per se [12,13]. Additionally, patients will complete the Kurzfragebogen zur aktuellen Beanspruchung (KAB; German for “short questionnaire for acute stress”), which will be repeated perioperatively multiple times to assess changes in response patterns [14]. The focus will be on individual stress trajectories and differences between the control and intervention groups.

For a more objective measurement of stress, the cortisol level in the serum is measured by taking blood samples at multiple times (at baseline, arrival in the operation room, skin incision, clamping the carotid artery, skin suture, and 1 hour after skin suture). Baseline measurements are all taken under consistent conditions: the same time of day before the patient rises from bed. Resting heart rate, KAB score, and the Richmond Agitation-Sedation Scale (RASS) score will be evaluated simultaneously with blood sampling. Cortisol levels are a common tool to measure stress in acute situations [15-17]. The RASS, commonly used in anesthesiology and intensive care, will be used to estimate patients’ agitation and provide insight into their stress levels [18]. Heart rate and RASS scores serve as objective measures of patient stress, while the KAB reflects patients’ subjective burden across 6 categories. This score is frequently used in psychology to capture current stress levels and is well suited for perioperative use due to its ease of administration. The differences in serum cortisol levels between the groups are considered the primary end point. All other measurements are secondary end points.

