#### Clinical Outcomes

In addition to patient satisfaction, anxiety before and during surgery will be assessed. Comparison of patient satisfaction and anxiety measures between the intervention and control groups will be conducted. Additionally, patients in the intervention group will be asked at the end of the operation day whether they would choose to use the goggles again during potential follow-up surgery. For these patients, the average STAI score will be compared between those who would opt to use the goggles again and those who would not. Furthermore, comparisons of the recorded vital parameters and scores at different time points during surgery will be made between the control and intervention groups.

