### Planned Analysis

The analysis will be conducted using SPSS. Due to the study’s exploratory nature, descriptive statistics will be applied. Appropriate measures of central tendency and variability will be used depending on the level of measurement. Graphical representations will be made using line graphs or box plots.

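### The article declares a focus on individual KAB trajectories, but the analysis it describes names only group comparisons by time point and gives the pre-operative KAB no stated role

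*Protocol article*

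**What the plan says.** All references are to the protocol article.

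- **Assessment of Distress** introduces the KAB as a questionnaire "which will be repeated perioperatively multiple times to assess changes in response patterns" and adds: "The focus will be on individual stress trajectories and differences between the control and intervention groups".
- The same section describes the pre-operative KAB in two ways. It is among the forms completed before the operation: "The day before surgery, after they provide informed consent, the patients will complete initial questionnaires". It is also tied to each blood sample: "Resting heart rate, KAB score, and the Richmond Agitation-Sedation Scale (RASS) score will be evaluated simultaneously with blood sampling". The blood samples include a baseline one, and "Baseline measurements are all taken under consistent conditions: the same time of day before the patient rises from bed".
- **Clinical Outcomes** describes the score analysis as follows: "comparisons of the recorded vital parameters and scores at different time points during surgery will be made between the control and intervention groups".
- **Planned Analysis** says: "Due to the study’s exploratory nature, descriptive statistics will be applied". It names central tendency, variability, and line graphs or box plots.
- **Strengths, Limitations, and Dissemination** speaks of comparing the groups on parameters recorded before, during and after the operation.
- Serum cortisol is the primary end point, so the KAB is secondary. The target is 100 patients, 50 per arm, without blinding.

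**The concern.** A focus on individual trajectories implies a quantity formed within each patient, or at least a comparison that takes account of where each patient started. The described analysis names neither. Group summaries at successive time points cannot tell a habitually tense patient from one who has become stressed in the operating room if their intraoperative scores agree.

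Two things are at stake. First, stable differences between patients stay in the comparison and widen its uncertainty. Second, a chance difference in pre-operative KAB between two arms of about 50 is partly carried into the apparent effect of the goggles. The KAB is the only patient-reported stress measure taken repeatedly, the Discussion summary says the study will evaluate whether the goggles reduce patient-reported stress, and choosing parameters for a later trial is a stated aim. A blurred KAB comparison serves that aim less well than the data allow.

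**Working it through.** **Text check.** The declared focus has two parts.

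| Part of the focus | Where the described analysis addresses it |
|---|---|
| Differences between the groups | Clinical Outcomes: comparison of scores by time point |
| Individual trajectories | No named summary: no change from baseline, slope, area under the curve or baseline adjustment |

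The scope in time also differs. Clinical Outcomes restricts the score comparison to time points during surgery. Read literally, that leaves out the pre-operative KAB and the one taken 1 hour after skin suture. The Strengths section includes times before and after the operation.

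**Size.** The plan gives no KAB figure to reproduce: no SD, effect, alpha or power. The following is for scale only.

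Inputs: n = 50 per arm (Randomization). Assumptions: a two-sided 95% interval, equal SD at both times, and a correlation r between pre-operative and later KAB. Results are in SD units.

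- Unadjusted difference at one time point: 1.96 × √(2/50) = 1.96 × 0.20 = 0.392.
- Adjusted for baseline (ANCOVA, large-sample): 0.392 × √(1 − r²).
- Plain change from baseline: 0.392 × √(2(1 − r)).

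| Assumed r | Unadjusted | Baseline-adjusted | Change score |
|---|---|---|---|
| 0.3 | 0.39 | 0.37 | 0.46 |
| 0.4 | 0.39 | 0.36 | 0.43 |
| 0.5 | 0.39 | 0.34 | 0.39 |
| 0.7 | 0.39 | 0.28 | 0.30 |

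For example, at r = 0.5 adjustment gives 0.392 × √0.75 = 0.339. At r = 0.3 the change score gives 0.392 × √1.4 = 0.464.

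Because 1 − r² never exceeds 1, adjustment does not lose precision in large samples. The change score is worse than no adjustment whenever 2(1 − r) > 1, that is, when r < 0.5.

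**Chance imbalance.** The standard error of a baseline difference between arms is √(2/50) = 0.20 SD. A gap larger than 0.20 SD in either direction therefore has probability P(|Z| > 1) ≈ 0.32, about one trial in three. An unadjusted later comparison carries about r times that gap. At r = 0.5, a gap of 0.20 SD adds about 0.10 SD to the apparent effect, in either direction.

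**The case against.** A reader might infer that the pre-operative KAB is never used and that the trajectory focus is abandoned. The documents do not support that. The KAB is repeated expressly to assess change. Line graphs can show individual courses. The Strengths section counts pre-operative time points in the group comparison, and no sentence excludes the baseline value. The sentence in Clinical Outcomes is generic and does not say how values enter the comparison, and the group-difference half of the focus is addressed. All of this stands, and it confines the point to what is named and what is not.

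It can also be said that the choice of summary for a secondary end point belongs in a full protocol or analysis plan, which is not shown. That lowers the weight of the point. It does not remove it, because the article does describe its analysis, and that description does not match the focus declared a few sections before.

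A third objection is that the precision gain comes from covariate adjustment and not from analysing trajectories, and that it rests on an assumed r. This is correct. Adjustment accounts for each patient's starting level; the individual courses themselves are shown only by individual lines. The fix therefore needs both.

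Finally, the baseline is not settled by the text. The day-before and before-rising KAB may be one measurement or two. Patients are randomized on agreeing to participate and complete the questionnaires after consent, in an unblinded trial, so the order of allocation and the day-before KAB is not stated. The schedule figure might settle this, but it is not available here. The documents give no ground for prescribing one of the two values outright.

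**Conclusion.** The point holds as a mismatch between declared focus and described analysis. The article announces individual KAB trajectories, names only group comparisons by time point with descriptive summaries, and assigns the pre-operative KAB no role in comparing the arms. It does not hold as a claim that the baseline is discarded or the focus cannot be met.

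The gain from adjustment is a 95% half-width of 0.36, 0.34 or 0.28 SD instead of 0.39 SD at r = 0.4, 0.5 or 0.7. At low r it is small. These figures assume 50 analysed per arm (exclusions would lower that number), equal SDs and a roughly continuous KAB.

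Severity is minor: the KAB is secondary, the study is an exploratory pilot without a sample size calculation, and no confirmatory KAB test is planned.

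**What to change.** 1. In Clinical Outcomes and Planned Analysis, state that the KAB during and after surgery is compared between arms with adjustment for the patient's own pre-operative KAB. Use either an ANCOVA at each time point or one repeated-measures model with arm, time, arm-by-time and the pre-operative KAB. Report exploratory estimates with 95% intervals and make no confirmatory claim.
2. Show individual patient lines by arm beside the group line graph.
3. State whether the day-before and before-rising KAB are one measurement or two. Name a single baseline, where possible one recorded before the patient knows the allocation.
4. Do not use a plain change score in place of adjustment.
5. Align the time points in Clinical Outcomes with those in the Strengths section.

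The cost is a few sentences and a standard SPSS procedure on data already being collected, with no new patients or measurements. The downside is that the KAB must be treated as approximately continuous, or a rank-based version used. Recruitment was about 90% complete at the article's final submission and the trial is unblinded, so the choice should be recorded before the KAB data are compared by arm.

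### Only the baseline cortisol sample is tied to a time of day, so change from the waking value mixes time of day with surgical stress, and the group comparison loses some precision if start times vary

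*Protocol article*

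**What the plan says.** Protocol article, Assessment of Distress, lists six blood samples for serum cortisol. For the first it sets a time-of-day rule: "Baseline measurements are all taken under consistent conditions: the same time of day before the patient rises from bed". The other five are placed by event: "arrival in the operation room, skin incision, clamping the carotid artery, skin suture, and 1 hour after skin suture". No clock time, start window or recording of the hour is stated for these five. The same section names the primary end point: "The differences in serum cortisol levels between the groups are considered the primary end point".

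Planned Analysis provides for descriptive statistics, with line graphs or box plots. Clinical Outcomes adds that recorded parameters and scores are compared between groups at the different time points. Neither section mentions adjustment for the hour of sampling.

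On the design, the Randomization section says: "The randomization scheme is constructed to ensure a 1:1 allocation ratio (50-50) upon reaching a total sample size of 100 patients". Sample Size Estimation says that "no formal sample size estimation was performed", so there is no stated precision or power target. Trial Design and Study Population says: "All patients scheduled for the abovementioned procedure who meet the inclusion criteria are informed about the study and invited to participate". It sets no limit on the hour of surgery, and it does not say how widely those hours vary.

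**The concern.** By fixing the hour of the baseline, the article accepts that cortisol depends on time of day. It then controls that source of variation in one sample of six. Two consequences follow, and they differ in kind.

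- **Within a patient.** A line from the waking value to incision or clamping shows the effect of hours passed since waking together with the effect of surgery. A fall could be taken for calm, or a flat line for lack of response, when part of the movement is time of day.
- **Between groups.** If operations start at different hours, some of the spread between patients at each event is due to the hour. That spread widens the interval for the primary comparison.

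This matters more here than in a trial with one fixed question. The second stated objective is to find out which parameters can measure a benefit, and Sample Size Estimation says the results are to serve as the basis for a confirmatory trial. Misread cortisol trajectories, or a cortisol SD inflated by unmodelled start times, would carry over into that trial.

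**Working it through.** The article gives no SD, effect size, alpha or power, so there is no figure of its own to reproduce. The check has two parts.

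**1. Change from baseline within a patient**

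Write cortisol at clock time t as D(t) + S, where D is the time-of-day component and S the response to surgery. Then

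change = [D(t_event) − D(t_waking)] + [S_event − S_waking].

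The first bracket is zero only if D is the same at both hours. Giving every patient the same start time makes the bracket the same for everyone, but does not remove it. This part needs no assumption about how start times vary.

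**2. Difference between groups at the same event**

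Under randomization, D(t_event) has the same expected value in both arms and cancels, so the expected bias is zero. What remains is added variance.

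Inputs:
- n = 50 per arm (Randomization section).
- SD at a fixed hour set to 1, so results are in SD units.
- Start times uniform over a window of w hours (assumption).
- Linear shift of b SD per hour, with b = 0.1 to 0.2 (assumption).

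Formulas:
- 95% half-width without clock-time variance: 1.96 × √(2/50) = 1.96 × 0.2 = 0.392 SD.
- Added variance: v = b²w²/12.
- Widening factor: √(1 + v).

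| Window w | v at b = 0.1 | v at b = 0.2 | Interval wider by |
|---|---|---|---|
| 0 h | 0 | 0 | 0% |
| 2 h | 0.003 | 0.013 | 0.2% to 0.7% |
| 4 h | 0.013 | 0.053 | 0.7% to 2.6% |
| 6 h | 0.030 | 0.120 | 1.5% to 5.8% |
| 8 h | 0.053 | 0.213 | 2.6% to 10.2% |

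Example: for w = 8 and b = 0.2, v = 0.04 × 64/12 = 0.213 and √1.213 = 1.102. The half-width becomes 0.392 × 1.102 = 0.432 SD.

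A simulation of 20,000 trials with w = 6 and b = 0.15 gave a mean between-arm bias of 0.002 SD, which is simulation noise. The standard error was 0.2068 against 0.2005 without clock-time variance, a rise of 3.1%. The formula gives √(1 + 0.0225 × 36/12) = √1.0675 = 1.033, in agreement.

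**The case against.** The best defence is that event-timed sampling is right for this question, since stress at incision or clamping can only be measured when they happen. The baseline is the one sample whose hour can be fixed, and fixing it is sound. The primary end point is a between-group difference under randomization and needs no change from baseline. The article condenses a fuller protocol, its timing figure is not available here, and covariate choice is often left to an analysis plan. All of this stands. It limits the point to how trajectories are read and to a modest, conditional loss of precision.

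A reader might infer more, and the documents do not support it:

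- **That surgery happens at any hour.** The article is silent on start times. If cases run in a narrow slot, the between-group loss is close to zero.
- **That the group comparison is biased.** A time-of-day shift common to both arms cancels in expectation. A chance difference in mean start time between arms is not a second harm. It is the same random error already counted in the wider interval.
- **That goggle cases are scheduled at different hours.** Allocation is open, but nothing links scheduling to arm. The article describes the small anesthesia team as a way to limit confounding.
- **That cortisol trajectories are the declared focus.** The sentence "The focus will be on individual stress trajectories and differences between the control and intervention groups" comes directly after the description of the repeated KAB questionnaire and before cortisol sampling is introduced.
- **That the loss is much larger.** A 30% share of variance due to clock time would widen intervals by 19.5%, since √(1/0.7) = 1.195. That needs v = 0.3/0.7 = 0.429, which over an 8-hour window means b = √(0.429 × 12/64) = 0.28 SD per hour, steeper than the slopes assumed above. The article gives no figure to support it.

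**Conclusion.** The point holds in limited form. Change from the waking baseline to any surgical event mixes time of day with surgical stress. This follows from the stated sampling rule, given the dependence on time of day that the article itself implies, and it does not depend on start times. The primary between-group comparison is not biased in expectation. It loses precision only if start times vary: from nothing for a single start time to about 10% wider intervals for an 8-hour window at the steeper assumed slope. The slopes and windows are assumptions, and the article supplies neither. No stated power or precision target is breached, because none is set. The reason to act is that cortisol is the primary end point, the stated analysis is unadjusted, and the remedy is cheap.

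**What to change.** With about 90% of patients recruited at submission of the article, the sampling need not change. The analysis can.

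1. Retrieve the clock time of operating-room arrival or skin incision for each patient from the anesthesia or laboratory record, and report its distribution by arm. The article does not say that these times are kept, so their availability is an assumption.
2. Beside the descriptive summary, give the between-group cortisol difference at each event with its 95% confidence interval, adjusted for that start time and for baseline cortisol. Use the start time and not the clock time of later samples, because the intervention could influence when those are taken.
3. State that change from the waking value is not a pure stress response, and base conclusions on group differences at the same event.
4. Show trajectories relative to the arrival sample only as a supplement, and only if that sample precedes goggle use.

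The cost is a little data retrieval and one extra covariate beyond baseline. No new samples or patients are needed. If start times turn out to be nearly the same for all patients, the adjustment will gain almost nothing, and the table of start times by arm will show this.
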